### Outcome measures

The primary study outcome will be the change in oral health status, which will be measured according to the children’s individual DMFT. The secondary outcome will be the CD4 count. The other important outcomes include the salivary pH level, number of cariogenic bacteria, debris index score, salivary flow, nutrition status (height and weight), overall or oral health-related quality of life, and frequency of daily oral care. Details are presented in the data collection section and Fig. 2.

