### Statistical analyses

Baseline and endline surveys will be conducted to assess changes in each outcome in both the intervention and control groups. To minimize overestimation of intervention impact, all intervention outcomes will be estimated with an intention-to-treat analysis. Initially, survey data will be stratified by different age groups: 3–5 years old, 6–11 years old, and 12–15 years old. Then, the data will be descriptively analyzed to assess the distributions of various factors related to the children and caregivers under the study. Next, bivariate analyses will be conducted to assess the correlations of each oral health indicator (DMFT, debris index, bacterial number, salivary pH, salivary flow, oral-health related quality of life) with different variables, using the chi-square test (or Fisher’s exact test when a count is smaller than five) for categorical variables, and Student’s *t* test for continuous variables. Then, we will apply a generalized estimating equation model [41] adjusted for basic demographic characteristics (e.g., sex) and factors identified as significantly associated with the outcome in the bivariate analyses. The statistical significance will be set at a *p* value < 0.05. All data analyses will be performed using IBM SPSS, version 24.0 (SPSS Inc., Chicago, IL, USA).

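### Covariates for the effect model are chosen by significance against the trial's own outcomes, with no limit to baseline variables, so the rule permits adjustment for what the intervention changes and does not assure adjustment for baseline DMFT or exact age

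*Protocol article*

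**What the plan says.** All references are to the protocol article.

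- **Data waves (Statistical analyses).** "Baseline and endline surveys will be conducted to assess changes in each outcome in both the intervention and control groups". The section commits to intention-to-treat estimates and first splits the data into age bands of 3–5, 6–11 and 12–15 years.
- **Screen (Statistical analyses).** "bivariate analyses will be conducted to assess the correlations of each oral health indicator" "with different variables, using the chi-square test" or Fisher's exact test for categorical variables, and a t test for continuous ones. The indicators are DMFT, debris index, bacterial number, salivary pH, salivary flow and oral health-related quality of life. CD4, the secondary outcome, is not among them.
- **Effect model (Statistical analyses).** "we will apply a generalized estimating equation model", "adjusted for basic demographic characteristics (e.g., sex) and factors identified as significantly associated with the outcome in the bivariate analyses". The significance level is p < 0.05. Sex is the only covariate named, as an example.
- **Variables measured.** Outcome measures defines the primary outcome as change in DMFT. Among the other outcomes it lists salivary pH, cariogenic bacteria, debris index, salivary flow, nutrition, "overall or oral health-related quality of life, and frequency of daily oral care". Questionnaires adds oral health knowledge, attitudes and perceptions of children (aged 6–15) and caregivers. Data collection places the comparison of outcome indicators at baseline and endline.

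**The concern.** The protocol fixes a selection rule here, and an analysis plan that followed it would carry the rule forward.

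The intervention consists of education sessions and supervised daily oral care. Endline oral care frequency, knowledge, plaque and bacterial count are steps by which it would reduce new caries. They are plausible predictors of DMFT, so a significance screen open to endline data would tend to pick them up. A model conditioning on them estimates only the effect that does not run through them. That is not the total effect an intention-to-treat analysis is meant to give, and when the indirect effect has the same sign as the total effect, the estimate moves toward zero.

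Two lesser matters follow from the same rule. The covariate set is unknown until outcomes have been seen, which leaves the primary model open to the data. And baseline DMFT and exact age enter only if they are offered to the screen and pass it, or if age is taken as a basic demographic.

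**Working it through.** **Inputs.** From Sample size: effect 0.7 DMFT, SD 3.3 (cross-sectional, ages 8–15), 260 per group, about 10% attrition, hence 260 × 0.9 = 234 analysed per arm. Assumed, because the protocol gives no values: share of effect mediated, size of the mediator shift, and baseline–endline DMFT correlation ρ. SD 3.3 is applied at both waves. The protocol states no figure on covariate adjustment, so there is none to reproduce; whether 260 follows from its inputs is a separate matter.

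**1. Adjustment for a mediator.** In a linear model, if a share *m* of the total effect Δ runs through the variable, the adjusted estimate is Δ(1 − *m*):

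| *m* | Adjusted estimate |
|---|---|
| 25% | 0.70 × 0.75 = 0.525 |
| 50% | 0.70 × 0.50 = 0.35 |
| 75% | 0.70 × 0.25 = 0.175 |

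A simulation (1,000 trials per setting, 234 per arm, SD 3.3, ρ = 0.7, mediator shifted 0.5 SD by treatment) gave estimates of about 0.53, 0.35 and 0.18. The mediator passed a p < 0.05 screen in 80%, 99.6% and 100% of trials. With baseline DMFT in the model throughout, power fell from about 90% to 64%, 36% and 13%.

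The power loss depends on the assumed shift *s* (in SD units). With baseline DMFT in the model, the standard error is about √[3.3²(1 − ρ²) − (*m*Δ/*s*)²] × √(2/234) × √(1 + *s*²/4). For *m* = 50% and ρ = 0.7, 3.3² × 0.51 = 5.554 and √(2/234) = 0.0925:

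| *s* | *m*Δ/*s* | SE | 0.35/SE | Power |
|---|---|---|---|---|
| 1.0 | 0.35 | 0.241 | 1.45 | 31% |
| 0.5 | 0.70 | 0.214 | 1.63 | 37% |
| 0.2 | 1.75 | 0.147 | 2.39 | 67% |

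The shrinkage depends only on *m*; the power loss depends on *s* as well.

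**2. Precision from baseline DMFT.** The outcome is change, so a change-score analysis is the fair comparator. Residual SD is 3.3√(1 − ρ²) with baseline adjustment and 3.3√[2(1 − ρ)] for a change score. Two-sided power is Φ(0.7/[SD × √(2/234)] − 1.96). At ρ = 0.7:

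- adjusted: SD 2.36, SE 0.218, 0.7/0.218 = 3.21, power 89%
- change score: SD 2.56, SE 0.236, 0.7/0.236 = 2.96, power 84%

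| ρ (assumed) | Adjusted: SD, power | Change score: SD, power |
|---|---|---|
| 0.3 | 3.15, 67% | 3.90, 49% |
| 0.6 | 2.64, 82% | 2.95, 73% |
| 0.7 | 2.36, 89% | 2.56, 84% |
| 0.8 | 1.98, 97% | 2.09, 95% |

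**3. Would a useful baseline variable pass the screen?** With 468 children and a correlation of 0.2 with the outcome, Fisher's z is 0.203 × √465 = 4.37, and Φ(4.37 − 1.96) is about 99%. If offered as a candidate, it would almost always be selected.

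**The case against.** **The protocol does not say that endline variables will enter the model.** This stands. The text before the screen speaks of factors related to children and caregivers, which can be read as participant characteristics. Oral care frequency is listed as an outcome. The notebook seal and checklist counts are collected only in the intervention group, so they cannot be covariates in A versus B. A reader might infer that the plan intends to adjust for mediators; the documents support only that it does not rule this out.

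**Baseline DMFT and age are partly covered.** This also stands. Age is handled through three bands, and sex is given only as an example of the demographics, so age may be meant too. A GEE with both waves as responses would already use baseline DMFT, although the model form is not stated. A strong baseline predictor would usually pass the screen. Omitting baseline DMFT does not bias the randomised comparison. Nothing in the protocol ranks baseline DMFT or age as the strongest predictors, and measuring the loss against an endline-only analysis would overstate it, since the outcome is change.

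**Other inferences that do not hold.** The named tests might suggest that DMFT must be dichotomised, but a t test can compare numeric DMFT across a binary factor such as sex. Nor is it shown that selection makes the standard error materially wrong: in a simulation with 15 baseline candidates, the mean reported standard error was 0.212 against an empirical 0.214, with type I error 5.7%.

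What remains is the rule itself: outcome-driven and unrestricted as to timing.

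**Conclusion.** The concern holds as a weakness in a stated rule that should be corrected; it is not evidence that the primary estimate will be biased. If a variable changed by the intervention enters the model, the A-versus-B estimate shrinks by the share mediated: 0.70 to about 0.53, 0.35 or 0.18 at assumed shares of 25%, 50% and 75%. The direction does not depend on those shares, provided the indirect effect has the same sign as the total effect; the size does, and the power loss also depends on the assumed mediator shift.

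The lack of assured baseline adjustment costs precision only: about 89% against 84% power at an assumed correlation of 0.7, with a wider gap at lower correlations. These power figures rest on 234 analysed per arm and on the SD of 3.3 from children aged 8–15 applying to the whole sample at both waves.

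**What to change.** In Statistical analyses, replace the significance-based rule with a model fixed before endline data are seen:

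- DMFT: group A versus group B, adjusted for baseline DMFT, age and sex.
- CD4: group A versus group B, adjusted for baseline CD4, age and sex. The present screen covers only oral health indicators and gives no covariate set for CD4.
- No variable measured after randomisation enters any effect model.
- The bivariate analyses stay as description and do not determine the effect models.

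The cost is wording only. DMFT, CD4, age and sex are simple to supply from the planned baseline survey and clinical records, and sample size and visits are unchanged.

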### Monitoring

An intervention monitoring team will be formed as part of the research team. This team is responsible for monitoring of all implementation activities. All adverse events and unintended effects of intervention will be reported to the monitoring team. Access to all monitoring- related information will be limited to the monitoring team members.

## Ethics and dissemination

### Ethical considerations

This study has been approved by the National Ethics Committee for Health Research, Ministry of Health, Cambodia (289NECHR).

### Individual consent

The research assistants will obtain informed consent from all caregivers prior to the intervention, and assent to participate in the study will be obtained from all children. The caregiver’s consent will be recorded through a signature or thumbprint. Participants can withdraw from the study for any reason, and this will not affect the normal services received at any of the health facilities.

### Post-trial care

The intervention will be introduced to the control groups’ participants immediately when a positive impact is identified.

### Confidentiality of information

All information obtained through this study will be confidential. Access to information will be limited to research assistants for conducting interview and data entry management staff during the research period. Study records will be identified only by means of study identification numbers.

### Dissemination

The findings of this study will be disseminated through peer-reviewed journals and international conferences. Important protocol modifications will be communicated to the research ethics committee and trial registry.

## Discussion

Here, we have described a study protocol for a randomized controlled trial to evaluate the effectiveness of an oral health intervention program in improving oral health status, which in turn will improve the immunity and overall health status of children living with HIV in Phnom Penh, Cambodia. This trial aims to investigate how the improvement of oral health status can contribute to the improvement of overall health status in a cohort of children living with HIV, compared with their HIV-infected and HIV-uninfected counterparts who do not undergo the oral health intervention. If proven effective, this oral health intervention could be suggested as another means to delay the onset of AIDS in this population and would lead to the further encouragement of oral health interventions for children living with HIV.

However, the proposed study has some limitations. First, the intervention will target children living with HIV receiving ART. Therefore, we will not be able to distinguish between the effects of ART and that of the oral health intervention on CD4 count or oral health status. Second, samples will be recruited only at one national hospital, and therefore this is a potential source of sampling bias. However, this study has the potential to provide strong evidence regarding the effectiveness of an oral health intervention in an area concentrated with children with HIV receiving ART.

### Trial status

The trial was registered in the International Standard Randomized Controlled Trial Number Register on 17 January 2018 (ISRCTN15177479) (http://www.isrctn.com/ISRCTN15177479). Recruitment for intervention commences in February 2018 and will continue until April 2020.

## Abbreviations

AIDS: Acquired immune deficiency syndrome
ART: Antiretroviral therapy
DMFT: Decayed, missing, or filled teeth
HIV: Human immunodeficiency virus
PedsQL: Pediatric Quality of Life Inventory
